## Abstract

**Background:**

Improving the existent effective treatments of depression is a promising way to optimise the effects of psychological treatments. Here we examine the effects of adding a rehabilitation type of imagery based on exergames and dynamic simulations to a short behavioural activation treatment of depression. We investigate the acceptability and the efficacy of an exergame-augmented dynamic imagery intervention added to behavioural activation treatment and associated mechanisms of change.

**Methods and analyses:**

In a two-arm pilot randomised controlled trial, the acceptability and preliminary efficacy of an exergame-augmented dynamic imagery intervention added to behavioural activation treatment for depressed individuals will be assessed. Participants (age 18–65) meeting criteria for depression are recruited by media and local announcements. 110 participants will be randomly allocated to behavioural activation plus imagery group or to standard behavioural activation group. The primary outcome is depressive symptom severity (Beck Depression Inventory II) and secondary outcomes are anhedonia, apathy and behavioural activation and avoidance. The outcomes are assessed at baseline, mid treatment, posttreatment and 3-month follow-up. Moderation and mediation analyses will be explored. An intention-to-treat approach with additional per-protocol analysis will be used for data analysis.

## Introduction

Major depressive disorder (MDD) is a common mental health problem that results in severe impairment of the life of affected individuals [1]. Although there are several effective treatments of depression, their efficacy was challenged, only a moderate-small effect being evidenced after removing the existing research biases [2]. Estimates suggest that 59% of depressed patients do not even respond to psychological treatments (50% reduction in symptoms) and two thirds do not remit [2]. To this shortcoming it adds the high rates of relapse, recurrence, residual symptoms, and the fact that many affected individuals receive no treatment. It is estimated that after treatment, 30 to 50% of recovered patients are still troubled by residual symptoms and up to 75% of patients relapse [3]. Improving the treatment for depression has a major impact on global mental health and economy.

Finding efficient ways to treat depression has always been a preoccupation for both researchers and clinicians. Despite significant efforts, the efficacy of treatments for depression did not significantly improve in time [4]. Targeting new mechanisms and optimising the already effective interventions are promising solutions to advance the treatment of depression [5].

Mental rehearsal interventions are considered promising stand-alone or added-on treatments for depression [5–9]. Recently, the effect of imagery has been tested by adding imagery to behavioural activation treatment for depression. Behavioural activation treatment is one of the most effective and robust psychological treatments for depression [10, 11]. Although adding imagery interventions to behavioural activation brings great promise for improving the treatment of depression, there are several potential improvements for imagery interventions. Renner et al. [9] have recently pointed out the limitations of mental imagery interventions in depression: only individuals who vividly imagine actions benefit from intervention; depressed individuals have difficulties vividly simulating actions, not knowing the ingredients of a prospective mental rehearsal of actions.

We suggest that a major source of potential improvements for mental imagery interventions comes from paying more attention to the contribution of the ongoing states of the sensorimotor and affective brain systems (motor, affective, and visual) to mental simulations. Considering the characteristics of the sensorimotor and affective brain systems involved in the mental construction of those experiences results in several advantages for imagery interventions. First, the differences in the states of the sensorial, affective, and motor systems recruited for simulation should be considered during imagery interventions for depressed individuals. For instance, depressed individuals show large differences in the state of modality-specific brain systems, having attenuated excitation of the motor cortex [12, 13] and deficient recruitment of brain systems involved in positive affect [14], which may influence the effect of the interventions. Second, considering how particular imagery modalities (e.g., visual versus motor) are used during the imagery process in depressed individuals may show a significant advantage. Differences in using some modalities over others may result in differences in the effect of imagery over behaviour [15]. For instance, the recruitment of the motor brain in imagery and the effect of mental imagery on action largely depend on the success of using kinesthetic rather than visual imagery [16]. Depressed individuals have more impaired motor imagery than visual imagery and compensate for this deficit by using modalities, which may limit the impact of imagery interventions [17]. Third, adopting an understanding of the mental simulation of feelings as mental re-activation of body sensations in imagery intervention may also bring a significant advantage for intervention. Recent research showed that felt sensations in the body are core components of feelings [18, 19], they can be maintained as representations in working memory [20], they are attenuated in depressed individuals [21], and that prospective simulations of sensations felt in the body during feelings in positive situations are attenuated in individuals with high levels of depressive symptomatology [22].

Here we propose that we may use these advantages and significantly improve imagery interventions by focusing on enhancing the embodiment of mental rehearsal in imagery-based treatments for depressed individuals. A large body of research suggests that the effect of mental simulations on emotion and behaviour heavily depends on their embodiments, or the efficient recruitment of specific sensorimotor and affective modalities in mental simulations by attention, verbal, and memory controls [23]. For instance, when simulating and paying attention to visual details rather than proprioceptive sensations, one will recruit the visual cortex for action simulation rather than the interoceptive and motor cortex, and vice versa [24]. Mental rehearsal of action is efficient for action and affective control when it adequately recruits motor and affective simulations [25]. Depressed individuals have difficulties recruiting motor and affective brain areas in their thinking. Thus, to optimise imagery treatment for depressed individuals, one should enhance the recruitment of modal (motor and affective) brain systems in the mental simulation process. When deficiencies of the modal brain areas required for imagery simulations are stable alterations (i.e., cognitive deficits of cognition), the intervention should follow a rehabilitation approach similar to motor rehabilitation imagery used in patients with brain damage (e.g., damages due to stroke). We focus on two potential solutions for improving imagery based on embodied processes: exergames and dynamic imagery.

A promising way to support the embodiment of simulations of action in depressed individuals is by using remote kinematics in the form of exergaming (XboxKinect^™^ games). Previous research showed that using exergaming results in the augmentation of motor (kinesthetic) imagery [26–28], increased motor rehabilitation in stroke patients [29], motor learning [30] and it is efficient as a stand-alone intervention for the reduction of depressive symptomatology [31–34]. Furthermore, exergaming has an increased acceptability and feasibility in various populations [29]. Based on these results, using exergaming as a tool for motor rehabilitation of action cognition in imagery interventions for depressed individuals seems to be worth investigating.

Another promising solution came from dynamic imagery. Dynamic imagery, as opposed to static imagery (mental rehearsal of movement without overt movement) requires mimicry of simulated movements [35]. Previous research has shown a *dynamic superiority effect*, individuals remembering better moving rather than static stimuli [36]. Similarly, a dynamic superiority effect has been evidenced for imagery. In comparison with static imagery, dynamic imagery results in higher vividness of mental imagery [37] motor learning [35] and behavioural performance [38]. Moreover, the imagery deficits which are evidenced in static motor imagery tasks are not evident when a dynamic strategy of motor imagery is applied for the same population [39].

Given that imagery methods added to behavioural activation treatments are promising for the treatment of depression [6, 9] and that dynamic imagery and stimulation by remote kinematic may help overcome limitations of existing imagery interventions, we intend to test the effect of adding a dynamic imagery intervention augmented by exergames to a short behavioural activation treatment [40].

Starting from the idea that action cognition and motor imagery deficits are stable alterations in depressed individuals [41–43] we use a rehabilitation type of motor imagery intervention based on principles of rehabilitation of motor imagery for individuals with neurological conditions. To this end, we integrate forward modelling of action and motor imagery [44], remote kinematics (Kinect) and embodied cognition account (action support of mental simulations, [25, 45]. This intervention is a new one that proved efficient in clinical work ([name], [Unpublished protocol]), [46]. There are several steps in the intervention. In the first session, the therapists introduce the *dynamic simulation routine*: how to support mental imagery of activities through gestures, language, and attention. Then, the patients undergo an exergame for 5 to 10 minutes and an “actfulness” exercise focusing on feelings of movement and motor simulation. After the exercise, the participants dynamically imagine a planned activity. In session two, patients are thought to restructure action memories by focusing on movements. Deficient action simulations are rehabilitated by (a) partial movements (they alternate covert with dynamic-partial movements simulations in response to stimuli); (b) linguistic supports (training in gerundival perceptions that is to recognize and name stimuli by actions; for instance, a door is recognized as a door to open; [47]), (c) enhanced perceptual and affective simulations (PETTLEP system, [48]), and (d) episodic memory support (they have to form future memories of *action cores*-last sequence of movement before perception of desired environmental change, correct them by experience, and remember at the end of the day). Thus, it is a rehearsal training that mixes actual and mental practice [49, 50] with augmentation of the motor component of simulations in thinking by enhancing *gestures*, *language*, *and episodic memory* as controls of simulation, and is applied to promote the use of motor simulations in everyday life.

We expect that adding a dynamic imagery intervention will augment the effects of behavioural activation treatment (BA) on severity of depressive symptoms. Second, we investigate whether adding the dynamic imagery intervention to behavioural activation treatment has any effect on secondary outcomes such as anhedonia, apathy, and vividness of imagery. Third, we investigate the moderators and mediators of the effects of the intervention.

## Methods and analysis

### Study design

The study is a two-arm phase II randomised controlled trial (RCT) with a parallel design to compare a short behavioural activation (BA) treatment with BA plus dynamic imagery enhanced by exergames (XboxKinect^™^). We recruit participants by online media, advertisements, and by contacting local psychiatrists. After the online screening and baseline assessment, participants are randomised to either BA or BA plus T-RAC. Then the participants are enrolled in the treatment. Participants complete a weekly assessment, one assessment of mediators at week six, one assessment after treatment and one assessment at three months. The consort flow for the Study is presented in Fig 1.

**Fig 1 pone.0288910.g001:**
[figure not shown]
The study flow.

#### Ethics and dissemination

This trial is approved by the ethics committee of the Faculty of Socio-Humanistic Sciences of University of Oradea (no: 2394/18.11.2022). Informed consent is required from participants before enrollment in the study. The results will be submitted for publication in peer-reviewed journals and presented at conferences.

*Trial registration number*. This trial was registered in the Clinical Trials Register: NCT05625230.

### Recruitment of participants

The recruitment of the participants will follow the CONSORT chart that will guide the flow of the participants. 110 participants will be recruited so that the study will have sufficient power to detect the differences at a 20% attrition rate. Participants will be selected through announcements about the study both online and at the local clinics. Participants are invited to complete an online screening questionnaire, including the PHQ-9 scale and questions for checking the eligibility criteria. Participants with a PHQ-9 score of ten or higher are programmed for the SCID-5-CV interview administered by telephone or face-to-face. Participants who are eligible will be randomly assigned (using Redcap) to one of the two groups: (1) behavioural activation (BA) or (2) BA plus rehabilitation of action simulations (BA Plus T-RAC).

Participants allocated to the behavioural activation arm will undergo a standard BA treatment. A therapist will administer the treatment for 8 sessions based on a manual built on the behavioural treatment protocol described by Martell et al. [51] and used in the COBRA trial [52]. Each session is focused on reviewing the activity log, discussing difficulties in the implementation of previously planned activities, planning “antidepressant” activities for the next week, and finding support for the implementation of the activity. Participants allocated to the BA plus T-RAC will undergo the same BA protocol plus an augmented imagery intervention. Each session is focused on reviewing the activity log, planning “antidepressant” activities for the next week, and finding support for the implementation of the activity. The difference is that after activity planning, the participant will follow Kinect for 10 minutes and will imagine one planned activity using actfulness. From session two, restructuring action memories are added.

### Eligibility

The inclusion criteria were age from 18 to 65, a score of 10 or higher on the PHQ-9 and a diagnosis of depression based on clinical interview. The exclusion criteria were: significant intellectual impairment; meeting criteria for a current psychotic or substance abuse disorder; history of mania/hypomania; significant changes in the dose of antidepressant medication during the past month; receiving psychological therapy; and the presence of suicidal intent.

### Management of suicidal ideation

We assess the suicidal ideation and intent at all assessments points of the study. Suicidal ideation is measured by the PHQ-9 item 9, BDI II, and clinical interview. If suicidal thoughts are reported, the C-SSRS interview is applied [53]. If suicidal intent (both unclear and clear) is identified the patient is not recruited in the study and contacted by phone by the clinical psychologist for proper recommendation to medical services. The participants with low risk suicidal ideation (suicidal ideation with no intent) are required to sign a non-suicide contract to continue the participation in the study. If suicide intent is identified, the participant is excluded from the study and necessary steps for medical assistance are followed (visit to psychiatrist, inpatient care). The suicide protocol is supervised by a licensed clinical psychologist.

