#### Secondary outcomes

*Depressive symptoms severity* is assessed with the Patient Health Questionnaire- 9 [57]. PHQ-9 scale contains nine items that measure the severity of nine depressive symptoms on a 4-point scale during the past two weeks. Each item is rated on a 4-point scale ranging from 0 (not at all) to 3 (nearly every day).

*Depression remission* is measured using The Structured Clinical Interview for DSM-5 Clinician Version [SCID-5-CV; 58], affective module at post measurement and follow-up. SCID-5 is a structured clinical interview used to determine the core diagnoses according to DSM-5 guidelines. Participants are considered remitted when they no longer fulfil diagnostic criteria for a major depression episode.

*Depression response* is assessed based on BDI II scores. To identify responders to treatment we compute the reliable change index. A reliable change index of more than 1.96 will classify a participant as a responder [59].

*Anhedonia severity* is assessed with the Snaith-Hamilton Pleasure Scale [60] SHAPS is a 14-item scale assessing the degree to which a person is able to experience pleasure or the anticipation of a pleasurable experience. Participants respond on a four points scale from strongly disagree to strongly agree. Each "disagree" response receives one point, whereas each "agree" response receives zero points. Thus, the final score ranges from 0 to 14.

*Apathy level* is assessed with the Apathy-Motivation Index [61]. AMI is a 18-item questionnaire used to identify three dimensions of apathy: Behavioural Activation (propensity to initiate goal-directed behaviour), Social Motivation (level of engagement in social interactions), and Emotional Sensitivity (feelings of positive and negative affection). Higher scores indicate greater apathy. Item scores are averaged to get scores for subscales and a total score (range 0–4) [61].

*Anxiety severity* is assessed with the Generalised Anxiety Scale 7 [GAD-7; 62]. GAD-7 is a self-report scale measuring the severity of generalised anxiety disorder (GAD) during the past 2 weeks. It contains seven items related to DSM criteria for anxiety. Participants respond on a 4-point scale. Each item is rated on a 4-point scale ranging from 0 (not at all) to 3 (nearly every day).

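### The suicidal-intent rule, applied as written after randomisation, ends outcome collection as well as trial treatment

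*Protocol article*

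**What the plan says.** The section on management of suicidal ideation sets the timing: "We assess the suicidal ideation and intent at all assessments points of the study". It then separates three situations.

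- Intent in a candidate: "If suicidal intent (both unclear and clear) is identified the patient is not recruited in the study".
- Ideation without intent: these participants "are required to sign a non-suicide contract to continue the participation in the study".
- Intent in a participant: "If suicide intent is identified, the participant is excluded from the study and necessary steps for medical assistance are followed". The examples of medical assistance are "visit to psychiatrist, inpatient care".

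Two places give the schedule. The abstract says "The outcomes are assessed at baseline, mid treatment, posttreatment and 3-month follow-up". Study design says "Participants complete a weekly assessment, one assessment of mediators at week six, one assessment after treatment and one assessment at three months". Under Secondary outcomes, remission is judged by the SCID-5 "affective module at post measurement and follow-up".

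Statistical analyses puts every randomised patient in the intention-to-treat analysis and handles missing data by multiple imputation. Nothing in the article distinguishes stopping treatment from leaving the study, or says that outcomes are still sought after exclusion for intent.

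**The concern.** The exclusion is from the study, not from treatment. Followed as written, a participant who develops intent during treatment has no posttest or 3-month BDI-II and neither SCID-5 remission assessment. A participant whose intent is first found at posttest loses only the 3-month values. Intent first found at 3 months loses no later scheduled visit.

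This missingness is created by the protocol and follows the outcome. Suicidal thoughts are screened partly through the BDI-II, which is the primary outcome instrument. The people removed are likely to be among those doing worst at that moment, and they are then sent to care that may change their course. Imputation has to guess that course from earlier scores and from participants who were not removed.

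The between-arm comparison is biased if the number excluded differs by arm, or if the error in their imputed values differs by arm. Equal numbers are not enough unless the errors are equal too.

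**Working it through.** **Does the rule reach randomised participants?** Intent is assessed at all assessment points, and Study design places these weekly, at week six, after treatment and at three months. Candidates with intent already have a non-recruitment rule. The exclusion sentence comes directly after the one on people who sign a contract to carry on in the study, and it speaks of a participant. If it covered candidates only, it would repeat the earlier rule. The plain reading is that it applies after randomisation.

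**The plan's sample size.** Inputs from Proposed sample size: d = 0.7, power 90%, dropout 20%. From Statistical analyses: two-sided alpha 5%. The noncentral t calculation gives 43.87, so 44 per arm (power 0.901). Inflating, 44/(1 − 0.20) = 55 per arm, 110 in total. The stated figures reproduce.

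**Possible bias in d.** The article gives no rate of post-randomisation intent, so the inputs here are assumed ranges. Let m1 and m2 be the numbers excluded in each arm, and r1 and r2 the mean true minus imputed posttest BDI-II in those participants, in SD units. With 55 analysed per arm:

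size of shift in d = |m1·r1 − m2·r2| / 55

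With the same r in both arms and r between −1.5 and +1.5:

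- imbalance of 1: at most 1 × 1.5/55 = 0.027
- imbalance of 2: at most 2 × 1.5/55 = 0.055
- imbalance of 4: at most 4 × 1.5/55 = 0.109

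The shift is 0 if r = 0, that is, if the imputed values are right on average. With equal numbers, 3 per arm, and r1 − r2 = 1, it is 3 × 1/55 = 0.055.

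**Scale.** The standard error of d is about √(2/55) = 0.191 with everyone observed and √(2/44) = 0.213 at the 44 per arm left after planned dropout. The three limits are then at most 0.14, 0.29 and 0.57 standard errors at 55 per arm, and 0.13, 0.26 and 0.51 at 44 per arm.

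**How much an on-treatment score helps.** A simulation used 55 per arm and 2,500 runs per setting, with regression imputation on the mid-treatment score standing in for multiple imputation. It assumed that excluded participants are 1.0 to 1.5 SD worse at mid treatment and that the mid-treatment score correlates 0.5 to 0.7 with posttest. The shifts in d were:

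| Exclusions by arm | Still 1.5 SD worse at posttest: arm with more exclusions looks better by | Back to average at posttest: that arm looks worse by |
|---|---|---|
| 2 vs 1 | 0.01–0.02 | 0.01–0.02 |
| 3 vs 1 | 0.02–0.04 | 0.02–0.04 |
| 5 vs 1 | 0.03–0.07 | 0.04–0.08 |

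The mid-treatment score shrinks the bias, but the sign depends on the unobserved course after referral.

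**Remission.** Each excluded participant is at most 1/55 = 1.8 percentage points of an arm's rate. An imbalance of 4 is at most 4/55 = 7.3 points.

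**Power.** If exclusions come on top of the 20% dropout, an assumed 2%, 5% or 10% leaves about 43, 41 or 38 to 39 per arm and power 0.89, 0.88 or 0.86. If the 20% already covers them, power is unchanged. Loss of power is therefore the lesser issue.

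**The case against.** **The end of data collection is inferred.** No sentence says assessments stop, and a condensed article may leave follow-up after discontinuation to the full protocol. It is indeed an inference, but it is the ordinary meaning of exclusion from a study, and the objection here is to a stated rule, not to missing detail. An analysis plan can choose the imputation model; it cannot supply values that staff were told not to collect.

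**The rule may concern entry only.** Eligibility lists suicidal intent as an exclusion, and the Discussion treats excluding high-risk people as a limit on generalisability. Both fit an entry rule. Neither limits the text on suicidal ideation, which runs across all assessment points and already has a separate rule for candidates.

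**More is observed than it seems.** The visit that triggers exclusion may itself supply a PHQ-9 or BDI-II score, even before mid treatment, and missingness that depends on recorded values can be handled by imputation. This has force and reduces the problem. It does not reveal what happened after psychiatric referral.

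**The numbers are small.** This stands. People with intent at entry are screened out, the more plausible imbalances shift d by only a few hundredths, and the trial is a pilot of preliminary efficacy. The case for change does not rest on a large expected bias.

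**Values collected after referral mix in other care.** Also true. How to use them depends on the estimand, but that choice is open only if the values exist.

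**Conclusion.** The concern holds. As written, the rule removes randomised participants from outcome collection for a reason related to the primary outcome, and intention-to-treat with multiple imputation only partly repairs this.

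The likely effect is small: at most 0.11 in d for an imbalance of 4 with a uniform 1.5 SD imputation error, and 0.01 to 0.08 in the simulated settings. It could go in either direction and could be zero. These sizes rest on assumed numbers of exclusions and assumed imputation errors, since the article gives neither. The reading itself rests on taking exclusion from the study literally, which gives medium confidence. The point is worth fixing because the loss is irreversible and avoidable at little cost.

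**What to change.** Amend the section on management of suicidal ideation so that exclusion from the study applies only before randomisation. For intent found after randomisation, keep all the clinical steps, stop or suspend trial treatment as clinically needed, and continue to seek the BDI-II and SCID-5 at the planned posttest and 3-month visits where consent and safety allow. If the sponsor already intends this, one clarifying sentence is enough to keep staff from applying the literal rule.

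The cost is a short amendment and follow-up contact with what should be a few participants, at visits already scheduled. No safety step is removed. Some acutely ill or hospitalised participants may still be missing, and the values obtained will include the effect of any psychiatric care received.
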